### Participant timeline {13}

Within the week before surgery, patients will visit the pre-medication outpatient clinic. Participants will be screened and, if eligible, will be asked to provide written informed consent to participate in the study. Only patients who provide consent will be included in the study. After obtaining consent, total height, weight, and waist to hip ratio will be measured. On the day of surgery, a preoperative lung ultrasound examination will be carried out immediately before the patient is admitted to the operating room. After induction of general anesthesia, patients will be randomized by opening a sealed envelope. The protocol is then carried out accordingly for the control group or for the intervention group. After extubation, patients will be transferred to the recovery room. A postoperative lung ultrasound examination will be carried out. Additional oxygen will be applied if oxygen saturation drops below 90% breathing room air. Patients will be discharged from the recovery room according to routine clinical criteria (oxygen saturation > 90% or similar to preoperative value breathing room air, hemodynamic stability, patient awake and oriented, sufficient pain control). Data collection ends after patient is discharged; no further follow-up is needed (Fig. 2).

**Fig. 2 Fig2:**
[figure not shown]
Patient timeline showing the different steps of the study process

### Sample size {14}

Sample size calculation was performed with G*power 3.1 Software [13]. Assuming a mean (± SD) ΔP of 10 (± 3) mbar at PEEP = 5 mbar and a mean ΔP of 8 (± 2) mbar at PEEP = BMI/3 mbar, *α* = 0.05, 1 − *β* = 0.8, G*Power yielded a required sample size of *n* = 54 (27 per group) patients. The anticipated effect size is based on the results previously published by Pereira et al. [10]. To compensate for refusal, technical difficulties, or possible dropouts, we will increase the sample size by 10%, resulting in a total sample size of 60 patients.

### Recruitment {15}

Recruitment in the pre-medication outpatient clinic will be continuously conducted by a member of the research team until the target randomized sample size of 60 participants is achieved. Based on current clinical case numbers, this will take approximately 6 months.

## Assignment of interventions: allocation

### Sequence generation {16a}

Randomization is performed by permuted block randomization with a 1:1 allocation ratio. Randomly permuted blocks of varying sizes will be used. The order within each block and the block order itself are randomly determined by one member of the research team with the help of www.randomizer.org. Said researcher will not participate in patient recruitment or data collection. All other research team members and participants are blinded to the randomization sequence.

### Concealment mechanism {16b}

To ensure that allocation is unbiased and concealed from patients and investigators, a numbered opaque envelope containing the group assignment is opened after induction of anesthesia by a data collecting member of the research team.

### Implementation {16c}

The allocation sequence is generated by an independent member of the research team who is not involved in screening or analysis. In envelopes prepared by the independent investigator, randomization is already established as described above and will be implemented after induction of anesthesia. Enrollment, clinical data collection, implementation to assigned allocation group, and monitoring of the procedure is performed by a data collection team.

## Assignment of interventions: blinding

### Who will be blinded {17a}

Trial participants will remain blinded to their randomized group assignment. However, due to the nature of the intervention, blinding is not feasible for clinicians performing the intervention, data collectors overseeing its implementation, and data analysts analyzing ventilator data, as readouts of respiratory and hemodynamic parameters inherently contain the implemented PEEP. Consequently, hemodynamic and respiratory data will be analyzed by non-blinded members of the research team. Given that this data is recorded on an ordinal scale, it is neither subject to interpretation nor distortion. The investigators evaluating the lung ultrasound data, on the other hand, will be blinded to the patient’s group allocation.

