### Outcomes {12}

The primary endpoint of this trial is the difference in driving pressure (ΔP) between the intervention and control group during general anesthesia in endotracheal intubation and volume-controlled ventilation (VCV). Secondary endpoints include:

Mechanical Power of ventilation (elastic-dynamic, tidal and total).Compliance of the respiratory system.Intraoperative fluid requirements.Average intraoperative vasopressor requirements (µg/kg/min).Number of intraoperative hypotension events (MAD < 65 mmHg for > 1 min).Time-weighted average of hypotension.Number of alveolar recruitment maneuvers (to be performed if SpO_2_ < 90% with FiO_2_ > 60%).SpO_2_ after arrival in recovery room (without oxygen insufflation).Number of patients with indication for oxygen insufflation (to maintain SpO_2_ ≥ 90%).Change in lung aeration score between before surgery and after arrival in recovery room(determined by lung ultrasound).Overall postoperative pulmonary complications.

For further clarification see, Table 1 (“Outcome Definition”).

**Table 1 Tab1:** Outcome definition

**Domain**	Respiratory mechanics	Rescue therapy	Hemodynamics	Postoperative status
Specific measures	• Driving pressure • Mechanical power of ventilation (elastic-dynamic, tidal, and total) • Compliance of respiratory system	• Number of alveolar recruitment maneuvers	• Intraoperative fluid requirements • Average intraoperative vasopressor requirements • Number of intraoperative hypotension events • time-weighted average of hypotension	• SpO_2_ after arrival in recovery room • Number of patients with additional oxygen insufflation^a^ • Change in lung aeration score
Specific metric	Difference between control and intervention group	Difference between control and intervention group	Difference between control and intervention group	Difference between control and intervention group
Method of aggregation	Mean + SD (parametric data) or Median/IQR (non-parametric data)	Mean + SD (parametric data) or Median/IQR (non-parametric data)	Mean + SD (parametric data) or Median/IQR (non-parametric data)	Mean + SD (parametric data) or Median/IQR (non-parametric data) and four-square table^a^
Time point	Intraoperative	Intraoperative	Intraoperative	Postoperative

Outcomes are defined following the framework of Saldanha et al. [20]

^a^Four-square table is only used as method of aggregation for “number of patients with additional oxygen insufflation”

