## Data collection and management

### Plans for assessment and collection of outcomes {18a}

Demographic data such as height, weight, and waist to hip ratio, as well as clinical data, which includes medication given, ventilation parameters, and vital data, are recorded on paper-based case report forms (CRFs, see appendix) by data collectors. Additionally, ventilator measurement data are exported electronically from the ventilator and hemodynamic data are exported electronically from the Philips monitoring. By duplicating the data collection (paper based + electronic), participation can be ensured even in the event of technical transmission or recording problems. Data collected on paper forms will be entered and then double checked by an independent researcher to ensure reliability and accuracy of the data.

To increase reliability and validity of the ultrasound examination, members of the research team will be trained in lung ultrasonography and solely these investigators will perform the examinations using a 1.5–6 MHz curved array probe (Vivid S70 N, GE Healthcare). To determine the secondary outcome “change in lung aeration score between pre- and postoperative lung ultrasound examination,” ultrasound data will be assessed by two trained investigators without knowledge of group allocation using the lung aeration score modified for perioperative setting [12]. The investigators are also trained prior to assessment to achieve optimal reliability and validity. To determine the primary and further secondary outcome, ventilator data and hemodynamic data will be analyzed by the data analyzing team as described below (20a).

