### Data management {19}

All participant information is stored in locked file cabinets and password-protected databases to which only research team members have access. Collected data are pseudonymized by a coded ID [identification] number. All records that contain names or other personal identifiers, such as informed consent forms, will be stored separately from study records identified by code number. Demographic and clinical data, as well as information on hypotension events and postoperative oxygen requirements, are recorded on paper-based case report forms (CRFs) and stored in locked file cabinets. Log files containing ventilator data are exported from ventilators and saved on a password-secured network drive. Hemodynamic data are exported from the Philips monitoring and secured on the same network drive. Ultrasound data are pseudonymized and stored on the ultrasound equipment and subsequently transferred to a password-protected network drive for further analysis. The clinical data will not only be recorded digitally, but also handwritten in case of possible technical problems or study protocol breaches.

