## Statistical methods

### Statistical methods for primary and secondary outcomes {20a}

The primary objective of the study is to determine whether BMI-adjusted ventilation strategies result in a reduction of driving pressure. Data are tested for normal distribution using the Shapiro–Wilk test. Differences between the intervention group and the control group are assessed with a two-tailed unpaired *t*-test for normally distributed continuous data and with the Mann–Whitney test for non-normally distributed continuous data. In addition, descriptive statistical analyses (mean ± standard deviation, median, interquartile range, and 95% confidence interval, if applicable) will be performed.

For secondary endpoints, to evaluate the changes in lung ultrasound score between the pre- and postoperative groups and between the intervention groups, a two-way ANOVA will be performed with the time point (preoperative/postoperative) as one independent variable and the study group (intervention/control) as the other independent variable. For categorical variables (hypotension events, number of patients requiring supplemental oxygen), Fisher’s exact test will be used. For the secondary endpoint “time-weighted average of hypotension events,” the area under the threshold of 65 mmHg (AUC) for each event will be calculated by summing the difference between MAP and the threshold, multiplied by the duration of the event. Total AUC will be divided by the observed time, which varies by patient. This results in a time-weighted average of hypotension per patient.

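### The reasons given for analysing driving pressure and haemodynamics unblinded do not hold, and masked final comparisons are feasible

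*Protocol article*

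**What the plan says.** Who will be blinded {17a} keeps patients and lung-ultrasound assessors blinded, but not clinicians, data collectors or the analysts of ventilator data. The reason given is that "readouts of respiratory and hemodynamic parameters inherently contain the implemented PEEP". From this it concludes that "hemodynamic and respiratory data will be analyzed by non-blinded members of the research team", and it adds as reassurance: "Given that this data is recorded on an ordinal scale, it is neither subject to interpretation nor distortion".

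Elsewhere the article describes the same data as follows:

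- Outcomes {12} defines the primary endpoint as the group difference in ΔP "during general anesthesia in endotracheal intubation and volume-controlled ventilation". Table 1 summarises it by mean and SD, or by median and IQR.
- Statistical methods {20a} uses a t-test "for normally distributed continuous data and with the Mann–Whitney test for non-normally distributed continuous data".
- Plans for assessment and collection of outcomes {18a} separates the sources: ventilator data come from the ventilator, while "hemodynamic data are exported electronically from the Philips monitoring". Paper forms are kept in parallel.
- Data management {19} says that demographic and clinical data, "as well as information on hypotension events and postoperative oxygen requirements, are recorded on paper-based case report forms".
- Methods to handle non-adherence and missing data {20c} removes a data set from the per-protocol analysis if the PEEP setting was not carried out or if ΔP is not evaluable.

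**The concern.** A plan may leave analysts unblinded if masking is impossible, or if the data leave them nothing to decide. Section {17a} claims both, and each claim conflicts with other parts of the article.

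The scale claim matters more, because it is the only safeguard {17a} offers for unblinded analysis of the primary endpoint. Even a correctly named scale says nothing about how values are extracted from a log, which source is used, or which data sets are dropped. The article itself contains at least one such decision: {20c} excludes patients whose ΔP is judged not evaluable. If that judgement is made with the arm known, it can favour one arm without anyone intending it.

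The feasibility claim is applied to both data types, although its reason fits only one of them. As a result, the haemodynamic safety comparisons lose masking that they could have had. These comparisons bear directly on whether a higher PEEP is tolerated.

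**Working it through.** **1. Scale of ΔP.** Inputs from Sample size {14}: ΔP 10 (SD 3) against 8 (SD 2) mbar, α = 0.05, power 0.80.

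- Pooled SD = √((3² + 2²)/2) = √6.5 = 2.55 mbar
- Standardised difference = 2/2.55 = 0.784
- Two-sided two-sample t-test (noncentral t): 27 per group, power 0.808
- 10% allowance: 54 × 1.10 = 59.4, rounded up to 60; 54/0.90 is also 60

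The plan's 54 and 60 are reproduced, so the sample size is not in question. The calculation uses means and SDs in mbar, which presupposes a continuous variable. Table 1 and {20a} agree with it. The hypotension formula in {20a} also multiplies a mmHg difference by a duration, which has no meaning on an ordinal scale. The ordinal label in {17a} therefore stands alone against {12}, {14} and {20a}.

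**2. Does each data item contain PEEP?**

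| Item | Where it comes from | Contains PEEP? |
|---|---|---|
| Raw ventilator log | Ventilator export | Yes. Control is 5 mbar and intervention BMI/3, which equals 5 only at a BMI of 15, so the log generally reveals the arm |
| Total mechanical power | Derived from the log | Yes |
| Derived ΔP, one number per patient | Plateau minus end-expiratory pressure | No. It is a difference, and neither component need be shown |
| MAP, hypotension events and time-weighted average | Patient-monitor export | No |
| Vasopressor and fluid requirements | Clinical record | No |

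The reason in {17a} covers the first two rows and not the last three.

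**3. What could still be decided with the arm known?** The article shows two places. One is the exclusion for non-evaluable ΔP in {20c}. The other is the choice between paper and electronic values, for which {18a} and {19} state no precedence rule. In particular, {19} places hypotension events on paper forms completed by collectors whom {17a} describes as unblinded, although the monitor export exists.

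**4. Sense of scale.** The document gives no bias size, so the shifts below are assumptions. Take no true effect, SD 2.55 and a systematic between-group shift b in derived ΔP. The noncentrality is (b/2.55) × √(n/2), with n per group. For b = 0.5 and n = 27 it is 0.196 × 3.674 = 0.72.

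| Assumed shift b (mbar) | Share of the 2 mbar target | Two-sided rejection, 27 per group | 30 per group |
|---|---|---|---|
| 0 | 0% | 5.0% | 5.0% |
| 0.25 | 12.5% | 6.4% | 6.6% |
| 0.5 | 25% | 10.9% | 11.6% |
| 1.0 | 50% | 29.3% | 32.1% |

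These are sensitivities and do not estimate what would happen in this trial.

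**The case against.** The strongest defence has four parts.

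- **Objectivity.** ΔP and MAP are read by devices. The word ordinal may be a slip for numerical or objective, and the article discloses unblinded analysis openly while blinding the outcome that most needs it, the image-rated ultrasound score. It stands that the data are fairly objective and any bias is likely to be small. Correcting the word does not rescue the sentence, however, because the step from scale to freedom from distortion fails for any scale.
- **Feasibility.** Whoever derives ΔP from the logs must handle PEEP and will generally see the arm. This stands for the derivation step. It does not extend to the final comparison, or to the monitor data at any step.
- **Paper as backup.** {18a} and {19} describe duplicate recording mainly as cover for technical failure. Hypotension has a stated threshold and duration in {12}, and its time-weighted average has a formula in {20a}. This narrows the room for choice but does not state which source takes precedence.
- **Scope.** A journal article condenses a longer protocol, and an analysis plan may exist. A reader might infer that the ΔP window, the breath selection and the within-patient summary are all left open to unblinded staff. The article does not support that: such rules are commonly fixed in documents not shown here, so their absence is not part of this point.

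Two other inferences also go too far. The article does not say that the people who derive ΔP are the same people who test it; it names only non-blinded team members and a data-analysing team. Nor does it suggest that repeated readings would enter the t-test as independent observations. The sample size counts patients, and that would in any case be a separate problem that masking does not cure.

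**Conclusion.** The point holds in a limited form. Section {17a} sets a rule, non-blinded analysis of both data types, on one reason that is wrong and one that is too broad. The contradiction over scale can be verified within the article and does not depend on any unseen document. The PEEP reason is sound for raw ventilator logs and total mechanical power, and unsound for monitor data and derived ΔP.

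The effect on the result cannot be quantified from the document and is probably modest. The rejection rates above rest on assumed shifts, the planning SDs and a null true effect. Unblinded clinicians and data collectors are unavoidable here and are not criticised, and the sample size is unaffected. The change is worth making because it removes a false assurance about the primary endpoint at little cost.

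**What to change.** 1. In {17a}, delete the ordinal-scale sentence. Limit the statement that blinding is infeasible to raw ventilator logs and to outcomes that contain PEEP, such as total mechanical power.
2. Derive one ΔP value per patient by script, over the period the protocol already states. The endpoint window is not redefined.
3. Derive hypotension events and the time-weighted average from the electronic MAP with the same script, using paper values only where the export failed.
4. Lock the script and all exclusion decisions, including non-evaluable ΔP under {20c}, before group codes are merged.
5. Pass the analyst a derived file without PEEP and plateau columns. Run the ΔP and haemodynamic comparisons under masked A/B labels, and analyse total mechanical power last.

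Replacement wording for {17a} could read:

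> Staff handling raw ventilator files cannot be masked, because these files show the PEEP setting. Driving pressure and haemodynamic outcomes will be derived by a script locked, together with all exclusions, before group codes are merged, and will be compared under masked group labels.

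The cost is a few hours of programming by the existing team. Masking stays imperfect for whoever handles the raw logs. No clinical procedure, endpoint or sample size changes.

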### Procedure for unblinding if needed {17b}

The data collection team is encouraged to maintain blinding as far as possible. The allocation will not be disclosed to the patient and to the lung ultrasound data analyzing team; nor will there be any written or verbal disclosure of the code in any of the corresponding non-pseudonymized patient documents. As the treating anesthesiologists are not blinded to group allocation, there is no need to establish an unblinding procedure.

## Data collection and management

### Plans for assessment and collection of outcomes {18a}

Demographic data such as height, weight, and waist to hip ratio, as well as clinical data, which includes medication given, ventilation parameters, and vital data, are recorded on paper-based case report forms (CRFs, see appendix) by data collectors. Additionally, ventilator measurement data are exported electronically from the ventilator and hemodynamic data are exported electronically from the Philips monitoring. By duplicating the data collection (paper based + electronic), participation can be ensured even in the event of technical transmission or recording problems. Data collected on paper forms will be entered and then double checked by an independent researcher to ensure reliability and accuracy of the data.

To increase reliability and validity of the ultrasound examination, members of the research team will be trained in lung ultrasonography and solely these investigators will perform the examinations using a 1.5–6 MHz curved array probe (Vivid S70 N, GE Healthcare). To determine the secondary outcome “change in lung aeration score between pre- and postoperative lung ultrasound examination,” ultrasound data will be assessed by two trained investigators without knowledge of group allocation using the lung aeration score modified for perioperative setting [12]. The investigators are also trained prior to assessment to achieve optimal reliability and validity. To determine the primary and further secondary outcome, ventilator data and hemodynamic data will be analyzed by the data analyzing team as described below (20a).

### Plans to promote participant retention and complete follow-up {18b}

N/a. No follow-up for clinically relevant outcome measurement needed.

### Data management {19}

All participant information is stored in locked file cabinets and password-protected databases to which only research team members have access. Collected data are pseudonymized by a coded ID [identification] number. All records that contain names or other personal identifiers, such as informed consent forms, will be stored separately from study records identified by code number. Demographic and clinical data, as well as information on hypotension events and postoperative oxygen requirements, are recorded on paper-based case report forms (CRFs) and stored in locked file cabinets. Log files containing ventilator data are exported from ventilators and saved on a password-secured network drive. Hemodynamic data are exported from the Philips monitoring and secured on the same network drive. Ultrasound data are pseudonymized and stored on the ultrasound equipment and subsequently transferred to a password-protected network drive for further analysis. The clinical data will not only be recorded digitally, but also handwritten in case of possible technical problems or study protocol breaches.

### Confidentiality {27}

Data are handled confidentially, and transfer of patient-related medical data is pseudonymized. No features are transferred that allow direct identification of specific participants. The subject identification code list to personal data is accessible only to the principal investigator. All further records containing names or other personal identifiers, such as informed consent forms, are kept separate from the study data identified by code number. Data collection, coding, security, and storage will comply with the provisions of the German Federal Data Protection Act (BDSG) and the EU General Data Protection Regulation (EU-GPDR). Accordingly records and documents related to the clinical trial will be kept for at least 15 years.

